#### Harms

All adverse events will be reported to the study coordinator regardless of a supposed relation to the trial intervention, who will in turn report all deaths and serious adverse events to the Central Committee on Research involving Human Subjects (CCMO) according to Dutch rules and legislation.

Being the primary outcome measure, DB was exempted of this reporting obligation. The relationship of all adverse events to the study intervention will be investigated by the primary investigators and the OAC. All adverse events will be followed until they have abated or until a stable situation has been reached.

#### Auditing

Based on the NFU standard for risk assessment and monitoring, each participating hospital will be visited by an independent monitor/auditor to audit adherence to the study protocol and to local research regulations. They will ensure correct handling of data and compare a random sample of the collected data to their source documents.

#### Interim analysis

An interim analysis of the primary endpoint will be performed when 50% of patients (*n* = 178) have been randomized and had 30 days of follow-up, aided by an independent statistician. The Haybittle-Peto approach is used to test efficacy, using symmetric boundaries at *p* < 0.001 to provide continuation or stopping advice. Finally, the steering committee will decide on the continuation of the trial.

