### Study end points

The primary outcome is the incidence of clinically significant DB, defined as anal blood loss occurring after the completion of the procedure necessitating emergency department consultation, blood transfusion, prolongation of hospital stay, re-hospitalization, or re-intervention (either repeat endoscopy, angiography or surgery) [5, 10, 20–23]. Self-limiting bleeding managed on an outpatient basis is not considered to be DB.

PC may improve patients’ health status, prevent serious complications of DB, reduce the demand for healthcare, and lower costs. The secondary outcomes therefore are (1) severity of DB (see Supplementary File 1 for definition of DB severity), (2) procedure time, (3) perforation rate, (4) EMR scar evaluation at the first surveillance colonoscopy after 6 months, (5) adenoma recurrence rate at 6 months, (6) health-related quality of life, and (7) direct and indirect costs related to PC.

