**Assessments:**							
***Collect baseline and procedure variables***	X	X	X				
***Collect primary outcome variables***			X	X			
***Standard of care surveillance colonoscopy***						X	
***Collect secondary outcome variables***						X	X

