### Monitoring

#### Data monitoring

According to the Dutch Federation of Universities (NFU) standard for risk assessment and monitoring, the trial was graded as having a negligible risk for participants. Therefore, no Data Safety Monitoring Board or Data Monitoring Committee was indicated. Nonetheless, a blinded OAC comprising 3–4 independent gastroenterologists will assess and weigh all severe adverse events after completion of the trial and decide whether these concord with definitions of the study endpoints. Using primary source data and blinded for treatment allocation (if possible), each member of the committee will individually evaluate the disease course of each patient. Disagreements will be resolved at a plenary consensus meeting. Only after consensus has been reached on each individual endpoint, a final analysis will be performed.

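### The only planned comparison by arm during enrolment covers delayed bleeding alone and holds harm to the efficacy threshold of p < 0.001, which would rarely flag even a doubling of bleeding

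*Protocol article*

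**What the plan says.** All places are in the Protocol article.

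- **Interim analysis.** The look is set at half of recruitment: "An interim analysis of the primary endpoint will be performed when 50% of patients". Those 178 patients must first complete 30 days, and a statistician from outside the trial team assists. The threshold is p < 0.001 in either direction: "The Haybittle-Peto approach is used to test efficacy, using symmetric boundaries at" that level. Advice to continue or stop follows from it. On who decides: "Finally, the steering committee will decide on the continuation of the trial".
- **Sample size considerations.** The two-sided 5% is split into 0.1% for the symmetric interim boundaries and 4.9% for the final test.
- **Data monitoring.** The trial was graded as negligible risk, so "no Data Safety Monitoring Board or Data Monitoring Committee was indicated". The blinded Outcome Adjudication Committee weighs severe adverse events once the trial is complete.
- **Harms.** All adverse events go to the study coordinator, who passes deaths and serious events to the national committee (CCMO). The primary investigators and the adjudication committee examine their relation to the intervention. However: "Being the primary outcome measure, DB was exempted of this reporting obligation".
- **Study end points.** Perforation is the third secondary outcome.

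**The concern.** A trial without a monitoring board has to get its protection against harm from other arrangements. Here, the only stated moment during enrolment at which the two arms are set side by side is the interim analysis, and it looks at one endpoint. Three features limit what it can show.

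1. It does not compare perforations, deaths or other serious events by arm. Case-by-case reporting can show that an event happened. It does not show whether such events are gathering in one arm.
2. Delayed bleeding does not pass through the serious-event route to the national committee. For an excess of bleeding in the clip arm, the interim analysis is the only external check that the article describes.
3. The boundary is symmetric. A very strict threshold for benefit protects the type I error and avoids stopping early on unstable evidence. Those reasons do not carry over to harm, because a review prompted by harm cannot produce a false claim of benefit.

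At stake is whether the steering committee, which takes the decision, would be alerted to a material excess of harm halfway through recruitment.

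**Working it through.** **Inputs**

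- Interim size: 178 patients, allocated 1:1, so about 89 per arm (Interim analysis; Randomization and treatment allocation).
- Control bleeding risk: 9.8%; clip-arm risk under the design: 2% (Sample size considerations).
- Interim boundary: two-sided p < 0.001, symmetric (Interim analysis).
- The article does not name the interim test. Fisher's exact test and the uncorrected chi-square test are both used as assumptions.

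**Step 1: the plan's own sample size.** For 9.8% v 2%, two-sided alpha 4.9% and 155 per arm, the exact power of Fisher's test is 80.2%. This reproduces the stated 310 patients. The pooled normal approximation gives 286 and the continuity-corrected one 336. The stated rates are therefore a sound basis for what follows.

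**Step 2: what the harm boundary demands.** The expected number of control bleeds is 89 × 0.098 = 8.7, say 9. For y clip-arm bleeds the chi-square statistic is

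z = [(y − 9)/89] / √[p̄(1 − p̄) × 2/89], with p̄ = (y + 9)/178,

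and p < 0.001 needs z > 3.29.

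- y = 26: p̄ = 35/178 and z = 3.21, not crossed.
- y = 27: p̄ = 36/178 = 0.202, z = 0.2022/0.0602 = 3.36, crossed.

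So the chi-square test needs 27/89 = 30%. Fisher's test needs 28/89 = 31%. Either is about three times the control count.

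**Step 3: chance of reaching the boundary.** Sum the product of the two binomial probabilities (89 per arm) over all tables that favour control with p below the threshold. The control risk is 9.8% throughout.

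| True clip-arm risk | p < 0.001, Fisher | p < 0.001, chi-square | p < 0.05, Fisher | p < 0.05, chi-square |
|---|---|---|---|---|
| 9.8% (no effect) | 0.02% | 0.04% | 1.5% | 2.5% |
| 19.6% (doubled) | 4.8% | 6.6% | 38% | 46% |
| 29.4% (tripled) | 46% | 51% | 89% | 92% |

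If clipping doubled bleeding, the planned boundary would stay silent in about 93% to 95% of trials. Even if it tripled bleeding, crossing would be close to a coin toss.

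**Step 4: is a formal test of perforation worth adding?** The documents give no perforation rate. Assume 0.5% in controls and 1% to 5% with clips. At 89 per arm, Fisher's test at p < 0.05 then has 0.02% to 21% power. A test would seldom signal, so a descriptive table is the sensible form.

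**The case against.** **Harms are not invisible.** A reader might infer that an excess of harm from clipping could not be seen while patients are still being enrolled. The Harms section does not support that. All adverse events reach the coordinator, deaths and serious events go to the national committee, and relatedness is examined. Treating physicians also know the allocation. What is absent is a comparison by arm, not knowledge of the events.

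**Table 1 does not show that perforation data come only at 6 months.** The row "Collect secondary outcome variables" is marked at +6 months and close-out, and a reader might conclude that perforation would be missing at the interim. The row cannot be taken so literally. Quality of life and costs are secondary outcomes too, yet their questionnaires are scheduled from the EMR onward, and procedure variables are collected at the EMR. Adverse-event reporting is a separate route again.

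**A symmetric Haybittle-Peto rule is recognised** and agrees with the 0.1%/4.9% split. It yields advice only, and the steering committee may act on less. Doubled bleeding would also run against the evidence in the Background. All this is right: the rule is neither an error nor a contradiction. It remains a stated rule that is a poor alarm for harm.

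**Perforation is a weak case for a test.** Randomization follows the resection, and clipping for an earlier perforation is an exclusion. Step 4 bears this out, and it is why only a table is suggested.

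**The article is condensed, and time has passed.** The full protocol may describe safety tables. By the Trial status section 217 patients had been randomized, more than the 178 that trigger the look, so the change may come too late for it. Both points lower the weight of the concern. The endpoint and boundary of the look are nevertheless stated in the article, and the point rests on those.

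**Conclusion.** The concern holds in a limited form, as a suggestion. Individual adverse events are reported during the trial, but the only comparison by arm that the article plans during enrolment covers delayed bleeding and judges harm at p < 0.001. The boundary needs 27 or 28 clip-arm bleeds against 9. It would be crossed about 5% to 7% of the time if clipping doubled bleeding, against 38% to 46% at p < 0.05.

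The figures assume 89 evaluable patients per arm, a control risk of 9.8%, and an unadjusted Fisher or chi-square test. The planned mixed model could move them somewhat. Doubling is an illustration, not a forecast.

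The documents do not support saying that harm would go unseen, that perforation data are unavailable before 6 months, or that the committee would be bound to continue.

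**What to change.** In the Interim analysis section:

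1. Keep p < 0.001 as the boundary for efficacy.
2. Replace the mirror-image harm boundary with a non-binding trigger for steering-committee review at a less extreme level, for example two-sided p < 0.05 in the direction of more bleeding with clips.
3. Have the independent statistician add a descriptive table by arm of perforations, deaths and all serious adverse events to 30 days, drawn from the events already reported to the coordinator. State that the continuation advice takes it into account. The table matters because even the p < 0.05 trigger would miss a doubling of bleeding more often than not.

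If the look has already taken place, the table can still be supplied from the existing data.

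The cost is one more table from a statistician already engaged, and a 1.5% to 2.5% chance of an unnecessary review if clipping has no effect on bleeding. The efficacy error is unchanged, because a review in the harm direction cannot lead to a claim of benefit. No monitoring board, extra visit or extra patients are needed.

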## Discussion

The CLIPPER trial has been designed to determine whether PC is effective in preventing clinically significant DB after EMR of large proximal colorectal polyps. The current study design was improved by considering and discussing potential drawbacks of published or ongoing trials with the principal investigators. The following suggestions were made and implemented in the CLIPPER study design:
Randomization after EMR. In this way, non-radical EMRs are not included in the intervention arm and therapeutic clipping for perforation or intraprocedural bleeding can be performed to the discretion of the endoscopist without causing cross-over. The reasons for exclusion of a non-randomized patient after informed consent are registered [32].Inclusion of patients with only one polyp, instead of multiple, enables one to estimate the pure effect of PC on DB and its severity [32].Inclusion of only right sided polyps, which are shown to be associated with a higher DB rate and significant decrease of DB after PC [32, 33].Inclusion of polyps sized 20–60 mm. Previous studies have shown no effect of PC for smaller polyps [34–36], and polyps over 60 mm were excluded in view of feasibility of complete closure [33].Cost-effectiveness analysis. Some studies have predicted cost-effectiveness of PC based on economic models [37, 38]. We will analyze cost-effectiveness based on healthcare utility questionnaires and clinical data.Follow-up period of 6 months. Previous studies have reported that clips can affect scar formation and cause clip artifacts that can be hard to distinguish from recurrent polyp tissue [14]. In order to determine these late clip effects, we included the first surveillance colonoscopy 6 months post-EMR in the follow-up period.

A potential drawback of this study is caused by the timing of the informed consent. In Dutch daily clinical practice, most polyps in the lower range of these inclusion criteria, especially the 2–3 cm polyps, will already be removed by EMR in the same session. As it would neither be ethical nor feasible to approach all colonoscopy patients for informed consent, we will likely include more 3–6 cm lesions undergoing repeat colonoscopy for EMR than 2–3 cm lesions. This needs to be taken into account when interpreting our results.

In conclusion, the CLIPPER trial is powered and designed to determine the efficacy and effectiveness of PC in everyday practice, in order to fill the gaps in our understanding of the place of PC in the endoscopy unit.

## Trial status

The first patient was randomized on May 15, 2018. To date, 19 hospitals are open for inclusion and 217 patients have been randomized. The inclusion is slightly below schedule, which is at least partly due to the recent COVID-19 outbreak. Protocol version 2.2 is being used and was approved on January 23, 2018, with an amendment approved on August 23, 2018. Patient recruitment is expected to last until mid-2021.

## Data Availability

The datasets generated and/or analyzed during the current study are available after publication from the primary investigator ([name]) on reasonable request.

## Abbreviations

EMR: Endoscopic mucosal resection
PC: Prophylactic clipping
DB: Delayed bleeding
NCCS: National Colorectal Cancer Screening Program
iFOBT: Immunological fecal occult blood testing
NBI: Narrow band imaging
APC: Argon plasma coagulation
ASA: American Society of Anesthesiology grade
LMWH: Low-molecular-weight heparin
DOAC: Direct oral anticoagulants
PI: Principle investigator
CRF: Case record form
QALY: Quality-adjusted life year
OAC: Outcome Adjudication Committee
(S)AE: (Severe) adverse event
METC: “Medisch Ethische Toetsings Commissie” (English: Medical Ethical Review Board)
CCMO: Central Committee on Research involving Human Subjects
NNT: Number needed to treat
ARD: Absolute risk difference
